### Sample size {14}

The DIG programme plans to reach 2700 households, of whom at least 15% of the project participants are people with disabilities, in line with the proportion of Ugandans living with a disability [9]. Thus, a minimum of 405 project participants are to be people with disabilities.

The sample size calculations are based on the effect of the intervention on the primary outcome among people with disabilities. The number of programme recipients, and consequently the size of the study, is fixed by the implementation partners’ funding. These calculations determine whether the study has sufficient precision to estimate the effect on per-capita expenditure in households with people with disabilities as the project participant.

Available data from the screening and verification visits informed the estimated total number of clusters that would be needed to reach 5400 eligible households. During the screening and verification process, BRAC Uganda found that approximately 25% of project participants were people with disabilities, and as such it was expected that the trial would include 675 people with disabilities in each arm. The distribution of eligible households per village was used to simulate the trial, 185 villages sampled with replacement from the verified villages gave approximately 5400 research participants in a simulated trial. A value of 0.8 was used from a recent evaluation of the graduation programme in Ghana for the standard deviation of the distribution of the normalised per-capita expenditure at baseline [10]. Since the degree of clustering in the outcome was unknown, the intraclass correlation coefficient (ICC) was allowed to vary between 0.05 and 0.3. The estimated between-village variation in mean level of the outcome at baseline and individual-level outcomes were drawn from the village-level means with a constant within-village variance. The endline results were generated using the simulated baseline data and a covariance matrix with a pre-post correlation of either 0.4, 0.6, or 0.8. The 185 clusters were pair-matched by the number of people with disabilities and a constant intervention effect was applied to the clusters allocated to the intervention arm. The intervention effects ranged from a difference between the intervention and control arms in the mean per-capita expenditure of zero standard deviations of the baseline per-capita expenditure, to 0.2 standard deviations, which is as high as the largest effects on per-capita expenditure observed in previous trials [1]. Multi-level linear regression was used to estimate the effects, controlling for baseline per-capita expenditure, accounting for clustering with a village-level random effect, and for the randomised design with fixed-effect for the pairs.

The results from the simulated analyses are shown in Fig. 3. The darker CIs correspond to scenarios with higher ICCs. Estimates were precise when the pre-post correlation was high (right-hand panel), and sufficiently precise to exclude the null with a low correlation and true effect of a difference between the arms of 0.1 standard deviation of per-capita expenditure at baseline (left-hand panel). Under conservative assumptions, we would reject the null hypothesis at conventional levels (*p* < 0.05) if the true effect of the intervention on per-capita expenditure was at least 0.1 standard deviations of the baseline distribution. This effect size is similar in magnitude to the overall effect on per-capita expenditure found in trials of the original (non-inclusive) version of the programme [1]; therefore, this trial would have sufficient power to detect an effect if the adaptations of the intervention for people with disabilities worked such that the effect was as strong as it had been for people without disabilities.

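### At 675 participants with disabilities per arm and a pre-post correlation of 0.4, power for a 0.1 SD effect is about 20-50%, so the protocol's claim of sufficient power is not supported

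*Protocol article*

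**What the plan says.** All of this is in the protocol article, Sample size {14}.

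- **Population.** "The sample size calculations are based on the effect of the intervention on the primary outcome among people with disabilities". The aim is to see whether precision is enough "to estimate the effect on per-capita expenditure in households with people with disabilities as the project participant".
- **Numbers.** "it was expected that the trial would include 675 people with disabilities in each arm", spread over 185 clusters. A minimum of 405 is also given for the programme's own recipients.
- **Simulation settings.** ICC from 0.05 to 0.3; pre-post correlation 0.4, 0.6 or 0.8; true effects from 0 to 0.2 baseline SDs. The analysis is a multi-level model with baseline expenditure as covariate, a village random effect and fixed effects for pairs.
- **Conclusion.** At the low correlation the estimates are called "sufficiently precise to exclude the null with a low correlation and true effect of a difference between the arms of 0.1 standard deviation". Under assumptions described as conservative, "we would reject the null hypothesis at conventional levels" if the true effect "was at least 0.1 standard deviations of the baseline distribution". It follows, the section says, that "this trial would have sufficient power to detect an effect if the adaptations of the intervention for people with disabilities worked" as well as they had for people without disabilities.

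No power percentage is stated. Size is said to be fixed by the implementers' funding.

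**The concern.** The conclusion is firm: at 0.1 SD the null would be rejected, even in the least favourable correlation setting. With 675 per arm and any realistic clustering, a 0.1 SD difference looks too small for that.

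The section treats 0.1 SD as the benchmark. It is described as similar to the pooled effect in earlier trials of the programme, worth about US$5 per person per month, and policy-relevant. If the trial has well under 80% power for that effect, a non-significant result is a likely outcome even when the adapted programme works as well as the original. A reader told that power was sufficient would then take that result as evidence that the adaptation failed for people with disabilities.

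**Working it through.** **Inputs, all from Sample size {14}:** n = 675 per arm; 185 clusters, so m = 1350/185 = 7.3 participants with disabilities per cluster; ICC 0.05 to 0.30; correlation r = 0.4, 0.6, 0.8; effect 0.1 baseline SD. The SD of 0.8 cancels when the effect is in SD units. **Assumed:** two-sided 5% test, equal arms, no attrition.

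**Formulas (baseline-SD units)**

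- SE = sqrt{ [2(1 − r²)/675] × [1 + (7.3 − 1) × ICC] }
- Power = Φ(0.1/SE − 1.96)
- Effect detectable with 80% power = (1.96 + 0.84) × SE

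Here ICC is the clustering left after baseline adjustment.

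**Trying to reproduce the stated conclusion.** Take r = 0.4 and no residual clustering. SE = sqrt(2 × 0.84/675) = 0.0499. The 95% half-width is 1.96 × 0.0499 = 0.098, so an interval centred exactly on 0.1 just excludes zero. Power is Φ(0.1/0.0499 − 1.96) = 52%. With ICC 0.05 the design effect is 1 + 6.3 × 0.05 = 1.315, the half-width is 0.112, and an interval centred on 0.1 includes zero. With ICC 0.30 the design effect is 2.89 and the half-width 0.166.

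**Full grid**

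| r | Residual ICC | SE | Half-width | Power at 0.1 SD | Detectable at 80% power |
|---|---|---|---|---|---|
| 0.4 | 0 | 0.0499 | 0.098 | 52% | 0.140 SD |
| 0.4 | 0.05 | 0.0572 | 0.112 | 42% | 0.160 SD |
| 0.4 | 0.30 | 0.0848 | 0.166 | 22% | 0.238 SD |
| 0.6 | 0 | 0.0435 | 0.085 | 63% | 0.122 SD |
| 0.6 | 0.05 | 0.0499 | 0.098 | 52% | 0.140 SD |
| 0.6 | 0.30 | 0.0740 | 0.145 | 27% | 0.207 SD |
| 0.8 | 0 | 0.0327 | 0.064 | 86% | 0.091 SD |
| 0.8 | 0.05 | 0.0375 | 0.073 | 76% | 0.105 SD |
| 0.8 | 0.30 | 0.0555 | 0.109 | 44% | 0.156 SD |

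At r = 0.4 the upper detectable effect, 0.238 SD, lies above the 0.2 SD that the section calls as high as the largest effects seen before.

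**Simulation of the protocol's model** (pairs, village random effect, baseline covariate). The section does not fully say how village effects carry from baseline to endline, so three versions were run at 675 per arm (ICC 0.05 / 0.30):

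| How endline is generated | r = 0.4 | r = 0.8 |
|---|---|---|
| Correlation r at both village and individual level | 39% / 22% | 70% / 43% |
| Endline = r × baseline plus independent noise (no residual clustering) | 49% / 49% | 85% / 85% |
| Village effect fully persistent | 45% / 35% | 87% / 88% |

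Other simulations with residual clustering, including runs with unequal cluster sizes, lower the bottom of the range slightly: to about 20% (r = 0.4), 25% (r = 0.6) and 39% (r = 0.8).

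**Participants needed for 80% power at 0.1 SD, r = 0.4, cluster size held at 7.3:** 1319 per arm with no residual clustering, 1734 at ICC 0.05, 3811 at ICC 0.30.

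**Alternative readings at r = 0.4 (ICC 0.05 / 0.30)**

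- 0.1 taken as raw units on an SD of 0.8, i.e. 0.1/0.8 = 0.125 SD: 59% / 31%, and 71% with no clustering.
- 405 per arm (the protocol gives 405 for programme recipients; the same number in control is assumed): 30% / 19%.
- All 2700 per arm: 73% / 26% by formula. In simulation, about 97% if baseline adjustment removes all clustering, and 88% / 46% if village effects persist fully.

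**The case against.** **Size is fixed by funding, the exercise is framed as precision, and no power figure is promised.** This explains why the number was not raised. It does not support the statements that the null would be rejected and that power is sufficient.

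**The lowest figures assume that the full ICC survives baseline adjustment.** The section describes village variation at baseline and then builds endline from the baseline data. It does not say that new village variation was added. This objection stands, and is why the range at r = 0.4 has to run up to about 50%. It does not bring any r = 0.4 case at 675 per arm to 80%.

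**The simulated trial had about 5400 participants.** If all were analysed, the claim could be true of what was simulated, but only under favourable clustering. It would then not answer the section's stated question about people with disabilities.

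Three stronger readings are tempting and are not supported:

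- *Power is at most about 52% whatever the assumptions.* That ceiling belongs to r = 0.4 only. At r = 0.8 power reaches 76% with residual ICC 0.05 and about 86% with none, so it is also not true without condition that a 0.1 SD effect would usually be missed.
- *The authors mistook an interval that just excludes zero for adequate power.* The 0.098 half-width makes this plausible, but Fig. 3 is not available to check it, and the 5400-participant explanation is equally open.
- *The change-score outcome in Statistical methods {20a} lowers power further.* Only if baseline expenditure is not among the adjusting covariates. If it is, the treatment estimate equals that of the baseline-adjusted model and nothing is lost.

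**Conclusion.** The claim is wrong as written for the population it concerns. With 675 participants with disabilities per arm and r = 0.4, power at 0.1 SD is about 20-42% if the stated ICC applies to the baseline-adjusted endline, and about 50% if no village clustering remains. None of the readings tried at that size and correlation reaches 80%. Over the rest of the protocol's grid, power is about 25-52% at r = 0.6 (63% with no residual clustering) and about 39-76% at r = 0.8 (86%). For 0.1 SD, 80% is reached only at high correlation with little or no residual clustering.

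The figures rest on a two-sided 5% test, equal arms and no attrition; any loss to follow-up would lower them. The cause of the discrepancy cannot be established from the text.

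**What to change.** In Sample size {14}, remove the statements that the null would be rejected at 0.1 SD under conservative assumptions and that power is sufficient. In their place:

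1. Give power at 0.1 SD, and the effect detectable with 80% power, for 675 participants with disabilities per arm at each stated r and across the ICC range.
2. Say how village effects carry from baseline to endline in the simulation, or show both cases. For example, at r = 0.4: power about 20-42% and a detectable effect of 0.16-0.24 SD with residual clustering; about 50% and 0.14 SD without.
3. State which participants the simulation behind Fig. 3 analysed: those with disabilities or all 5400.
4. State that a non-significant result will be interpreted from its confidence interval and not as absence of effect.

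The cost is wording only. No participants are added and the design does not change, but the stated power becomes less favourable.

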**Fig. 3 Fig3:**
[figure not shown]
Precision of estimates of effect using simulated data. Darker confidence intervals are from scenarios with higher levels of clustering

How big is 0.1 standard deviations in per-capita expenditure in real terms? Pooled analysis of studies in six countries shows that the 0.1 standard deviation effect on per-capita expenditure was equivalent to US$5 per-capita per month (adjusted for purchasing power parity [1]). In households with on average six members, this would amount to US$27 increased expenditure per month per household. Many ultra-poor families live on less than $US0.80 per person per day, and this would constitute an 18% increase in per-capita expenditure. In contrast, where available, disability allowances in Uganda amount to around $5 per person with disability per month [7]. Therefore, an effect of 0.1 standard deviations would be a substantial increase compared to other benefits.

An effect of this size would also have policy implications since it would likely mean that the programme was cost effective. Aside from Honduras (where there was a negative effect on expenditure), in previous studies the UPG programme had cost-effectiveness ratios between 133% in Ghana to 433% in India, based on the improvement in per-capita expenditure alone [1]. Such a result for people with disabilities would be important not only for the families involved, but also for motivating investment in an under-served population.

### Recruitment {15}

The implementing partners (BRAC, HI, and NUWODU) are responsible for selection of households to take part in the programme. Since the graduation model entails a large investment in participating households, accurate targeting of beneficiary households is important to avoid waste [11]. Selection into the programme is based on household-level indicators, and achieved by a two-stage process:

*Stage 1*: Selection of potentially eligible households. BRAC Uganda screens households in villages near to their branch offices in the target districts. Eligible households are identified based on the eligibility criteria, as earlier described.*Stage 2*: Verification of eligibility. Verification is completed by the project manager of the DIG programme. The project manager confirms that households meet the eligibility criteria, as earlier described.

The unit of participation in the programme is the household; however, a single individual within each household is the ‘project participant’ who is the main recipient of the training and assets. This person is expected to take responsibility for managing the enterprise and participate in other activities, such as training on enterprise management or savings group meetings. Project participants are selected before randomisation. The field worker and the household members discuss who is best suited to manage the enterprise and take part in the training. When discussing with household members who should be the participant, the fieldworkers encourage people with disabilities and/or women—usually spouse to the household head—to be the participants where possible even if they are not the head of household.

### Who will take informed consent? {26a}

For the evaluation, informed consent is obtained prior to each round of data collection. The informed consent process is conducted by the BIGD/IERC interviewer, trained in the informed consent process. Before taking informed consent, the interviewer provides hard copies and reads aloud the participant information sheet and consent forms to the participants. Consent and data collection procedures are adapted to support the participation of people with different impairments, such as sign language for participants with profound hearing impairments and knowledge of a standard sign language. Written informed consent is then obtained by means of participant-dated signature (or thumbprint) and dated signature of the person who presented and obtained the consent.

### Additional consent provisions for collection and use of participant data and biological specimens {26b}

Participants provide their consent for their data to be uploaded into a public repository and for it to be used in ancillary studies during the informed consent process (see Supplemental file 1 for model consent form). No biological specimens will be collected.

## Assignment of interventions: allocation

### Sequence generation {16a}

Randomisation is stratified by BRAC office branch, to ensure sufficient programmatic support to the clusters in the intervention arm, and pair-matched based on the number of people with disabilities. For each branch, clusters are ranked by the number of project participants who are people with disabilities. Adjacent clusters in the ranked lists are paired. Each cluster in a pair is randomly allocated to each arm using random number allocation in using Stata (StataCorp. College Station, TX: StataCorp LLC).

### Concealment mechanism {16b}

No concealment mechanism, clusters are randomly allocated using Stata (StataCorp. College Station, TX: StataCorp LLC).

### Implementation {16c}

Assignment of clusters to intervention and control arms is led by the implementing partners (BRAC, HI, and NUWODU) with support from IERC and BIGD, in order to meet the criteria for the evaluation. Allocation is conducted at one time point prior to the baseline survey and implementation of the DIG programme. The programme team pre-identified the desired number of intervention beneficiary households that each of the eight BRAC branches could support based on the sample size of 2700 households. This number ranged from 320 to 420 households.^1^ The number of eligible households, identified during the screening and verification process, within each cluster was calculated. Permutations of cluster allocation were then run in Stata, until the desired total number of 2700 households for the DIG programme was reached in the intervention arm. Remaining clusters were assigned to the control. In the end, 96 clusters were assigned to the intervention arm and the remaining 89 clusters to the control arm. Overall, 2898 households were assigned to the intervention arm while 2402 households were retained as control—the distribution of households by district and BRAC branch is shown in Table 2.

**Table 2 Tab2:** Distribution of households in control and intervention arms by district and BRAC branch

District	BRAC Branch	Number of Households		
		Control Arm	Intervention Arm	Total
Gulu	Gulu	367	355	722
	Lacor	288	340	628
	Goma	280	406	686
Nwoya	Anaka	366	370	736
Oyam	Minakulu	324	402	726
	Kamdini	285	357	642
	Loro	263	311	574
Kiryandongo	Kigumba	229	357	586
Total		2402	2898	5300

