### Trial design {8}

The overall effect of the intervention is estimated using a two-arm, parallel group, longitudinal, pair-matched cluster-randomised controlled superiority trial design. Clusters are defined as villages with 10–75 eligible households, within which households act as the observational unit (see ‘Eligibility criteria {10}’ section for further details).

The DIG programme has identified more than 11,000 eligible households, but only has funding to reach 2700 households under the programme. Randomisation is therefore an equitable way to select households for inclusion. It is also not yet clear that the intervention is effective for people with disabilities and their families. Cluster randomisation was chosen in part because of the nature of the DIG programme, which includes components delivered at the village level.

After random allocation of villages into intervention and control arms, but prior to implementation of the intervention, a baseline survey at household level is conducted (November 2020). The DIG programme is then implemented for 18 months from December 2020 to June 2022. Two endline household surveys are undertaken—the first in July 2022 for participants with a disability to determine the effects of DIG at programme end (endline 1); and a second one in October 2023 for all participants (endline 2), inclusive of participants with disabilities, to assess the longer-term differential effects of the DIG programme between households with and without disabilities.

This work is complemented by a process evaluation to further understand implementation of the DIG programme. The process evaluation is guided by theoretical considerations, such as What underlying theory are we testing with this intervention? What is the theory underlying the design of the graduation programme? And what is the theory underlying the adaptations to make them inclusive? These considerations ground the process evaluation in the relevant wider literature, and support generalisability to future intervention designs that draw on similar theories. To facilitate consideration of theory, an unambiguous articulation of project theory as supposed by the delivery team is developed iteratively in the form of a directed acyclic graph (DAG), based on the theory of change and using set rules for specifying how change is expected to happen.

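### The protocol gives two unreconciled accounts of how clusters were allocated, and the analysis names pair and district but not branch, the randomisation stratum

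*Protocol article*

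**What the plan says.** Trial design {8} calls the study a "two-arm, parallel group, longitudinal, pair-matched cluster-randomised controlled superiority trial design". Sequence generation {16a} gives the mechanism: "Randomisation is stratified by BRAC office branch, to ensure sufficient programmatic support to the clusters in the intervention arm, and pair-matched" on the number of participants with disabilities. Clusters are ranked within each branch; "Adjacent clusters in the ranked lists are paired", and "Each cluster in a pair is randomly allocated to each arm using random number allocation". Sample size {14} states that the simulation pair-matched all 185 clusters and analysed them with a village random effect and fixed effects for pairs.

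Implementation {16c} describes a different rule. Each of the eight branches had a desired number of intervention households. The account of how the intervention arm was filled is "Permutations of cluster allocation were then run in Stata, until the desired total number of 2700 households for the DIG programme was reached". For all other clusters it says "Remaining clusters were assigned to the control". The outcome: "In the end, 96 clusters were assigned to the intervention arm and the remaining 89 clusters to the control arm", with 2898 and 2402 households.

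Statistical methods {20a} fits a multi-level linear model to the change from baseline, adjusts for baseline covariate imbalance, and says that random intercepts and random exposure slopes will be considered for district and pair. Branch is not named, nor is a cluster-level term.

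**The concern.** Sending one cluster of each pair to each arm is one rule. Re-drawing until the intervention arm holds enough households is another. They can be combined, by re-drawing within pairs until a target is met, but the article does not say that this was done, and {16c} does not mention pairs. {16a} in turn mentions no household target and no rule for a cluster left over when a branch has an odd number.

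The analysis depends on which rule was run. If pairs are intact, a pair-level intercept plus an exposure slope distinguishes the two clusters of a pair, so the model carries both the matching and the clustering, and pair membership implies branch. If pairs were broken, many pairs hold two clusters of the same arm. The pair terms then neither separate those clusters nor describe the allocation, and the true stratum, branch, is represented only through four districts. An acceptance rule based on household numbers also makes the allocation depend on cluster size, which the model does not name.

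**Working it through.** **Inputs.** 185 clusters (Eligibility criteria {10}); eight branches, 96 and 89 clusters, 2898 and 2402 households (Implementation {16c} and its Table 2); target of 2700 intervention households ({16c}). Clusters per branch and the spread of cluster sizes are not given.

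**1. The plan's own totals.** 96 + 89 = 185. The branch rows of Table 2 add to 2402 + 2898 = 5300. Both agree with the text.

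**2. What pairing can produce.** One overall list gives 92 pairs and 1 leftover, so 93 against 92, which is not the reported split. With pairing inside branches, each branch with an odd count leaves one cluster over. Since 185 is odd, the number of odd branches k is 1, 3, 5 or 7, and the largest possible split is (185 − k)/2 + k against (185 − k)/2:

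| k | intact pairs | largest split |
|---|---|---|
| 1 | 92 | 93 / 92 |
| 3 | 91 | 94 / 91 |
| 5 | 90 | 95 / 90 |
| 7 | 89 | 96 / 89 |

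So 96/89 is attainable with every pair kept, but only if seven of eight branches were odd and all seven leftovers went to intervention (185 = 2 × 89 + 7).

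**3. Unpaired clusters.** 96 − 89 = 7, so at least 7 intervention clusters lack a control partner however the draw was made: 7/185 = 3.8% of clusters.

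**4. If pairs were ignored.** Drawing 96 of 185 at random, the chance that a given pair has one cluster in each arm is 2 × 96 × 89 / (185 × 184) = 0.502. Over 92 pairs that is about 46 (simulated 95% range 37 to 55). The article therefore leaves open whether there are 89 informative pairs or about half that number.

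**5. Cluster size.** Mean size is 2898/96 = 30.2 against 2402/89 = 27.0 households, a ratio of 1.12. To see how unusual this is, suppose 89 pairs were kept with fair within-pair draws and the 7 leftovers went to intervention. The expected intervention total is 5300 × 96/185 = 2750. With cluster-size standard deviation s, an assumption because the article gives none, the total equals 2650 plus half the leftovers plus half the sum of the within-pair differences. Its standard deviation is about s × √(89/2 + (7/4) × 178/185) = 6.8s. Simulation with sizes limited to the stated 10 to 75 gave:

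| assumed s | SD of total | P(total ≥ 2898) | P(total ≥ 2700) |
|---|---|---|---|
| 10 | 68 | 1.4% | 77% |
| 14 | 92 | 5.5% | 71% |
| 18 | 112 | 9.2% | 67% |

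The observed total is on the high side but not extraordinary. Under this scenario most draws would meet the 2700 target, so that rule alone constrains the allocation only mildly.

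**6. Precision.** The unequal split itself costs almost nothing: (1/96 + 1/89) / (2/92.5) = 1.001.

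**The case against.** The strongest reply is that {16c} merely completes {16a}: within-pair allocations were re-drawn until the household target was met, and unpaired clusters were placed in the intervention arm to help reach it. That is constrained randomisation, and it reproduces 96/89 exactly. The analysis section only says that pair-level effects will be considered, and with random effects unpaired clusters still contribute. Baseline covariates to be adjusted for include factors affecting implementation, which could cover cluster size, and a change-from-baseline outcome removes stable differences in expenditure between large and small clusters. The allocation is finished, and the article condenses a fuller protocol.

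Much of this stands. A reader might infer that 96 against 89 shows broken pairs; step 2 shows that it does not. A reader might add that seven leftovers all falling to intervention has probability 0.5^7 = 0.8%. That holds only if leftovers were coin-tossed, and the article does not say how they were handled. A reader might take 30.2 against 27.0 as proof of a systematic size effect; step 5 does not support that. Nor do the larger intervention household totals in seven of eight branches, which are expected if seven branches each gave that arm an extra cluster.

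What the reply does not remove is that the constrained-randomisation reading is supplied by the reader. The article states two rules, says in {14} that an odd number of clusters was pair-matched, and names district rather than branch in the model.

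**Conclusion.** The point holds as an unreconciled allocation procedure with a set of design terms that may not fit it. Three things hold on any reading: at least 7 intervention clusters have no opposite-arm partner, all 185 clusters cannot have been paired, and the household-total acceptance rule is not reflected in the named design terms, which also omit the branch stratum. Whether pairs were kept cannot be settled from the article. The number of informative pairs is at most 89 and would be about 46 if pairs were ignored.

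The size imbalance is suggestive only. A total of 2898 or more has probability of roughly 1.5% to 9%, assuming intact pairs, leftovers sent to intervention and a cluster-size SD of 10 to 18. No bias in the primary outcome is shown. The consequence is that the design terms of the primary model cannot be justified until the procedure is stated.

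**What to change.** First, reconcile Trial design {8}, Sample size {14}, Sequence generation {16a} and Implementation {16c} to what was actually run: whether pairs were preserved in each draw, the exact acceptance rule (the arm ended 2898 − 2700 = 198 households above target), how leftover clusters were handled, and the number of intact pairs, with clusters per branch and arm.

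Then align Statistical methods {20a}:

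- If pairs were kept, retain the pair terms and treat each unpaired cluster as its own unit within its branch.
- If pairs were not kept, replace the pair terms with branch fixed effects and a cluster random intercept, and adjust for the cluster-level number of participants with disabilities and number of eligible households.
- In either case, adjust for cluster size.
- If the allocation code can be recovered or rebuilt, add as a sensitivity analysis a randomisation test that re-runs the same procedure under the same acceptance rule.

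The cost is wording, one or two cluster-level covariates and some programming. Both variables were known from screening and verification before allocation, so no new data are needed.
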